#### Tertiary outcomes

These outcomes relate to patient and GP satisfaction with the treatment, the use of the PCT POC test, and the long-term follow-up. This will be measured in semi-qualitative studies.

### Analysis of procalcitonin

The PCT POC test (ThermoFisher Scientific® PCT Direct, Berlin, Germany) has a functional assay sensitivity (FAS) of 0,22 ng/mL, which is within target range of application in general practice.

The test has two parts: (1) a measuring device (immunochromatography) which analyzes the PCT level in 20 µl of blood (capillary); and (2) a device with a needle to take out 50 µl of blood from the finger and that can be placed directly into the measuring device. Analysis takes 20 min and the only discomfort for the patient is from taking the capillary blood sample from the finger.

#### Guidance for PCT levels

PCT levels are guided by current literature [16, 17, 26] as follows:

PCT-levels between < 0,25 ng/mL: low risk of bacterial etiology, antibiotic treatment will not be prescribed.PCT levels $$\ge$$ 0,25: bacterial etiology is more likely, antibiotic treatment will be prescribed

### Statistical methods

#### Data management

Data from the study in the form of Case Report Forms (CRFs), questionnaires and telephone interviews will be collected in Surveyxact and transferred to SAS (v. 9.4. Cary, NC, US) for analyses. Raw data will be anonymized in the practices before being imported into the data matrices by replacing names and civil registration numbers with study numbers as part of the randomization process.

Collection, storage and processing of data has been approved by Data Protection Systems (in Danish: “Datatilsynet”).

#### Sample size

A comparable study by Briel et al. [18] showed that the number of days when patients experienced restrictions from an ARTI had a standard deviation of 4 days. The PARI project’s non-inferiority design allows for a clinical non-important difference in sickness of max. 1 day in the PCT group compared to the standard care group. We expect an ARTI to last on average 9 days [21, 22]. The power (1-β) is set at 85% and α at 0.025 (non-inferiority study design). We believe these are relevant estimates since non-inferiority of a PCT-guided antibiotic treatment has previously been demonstrated [18, 19].

The two arms of the study will be randomized 1:1 with 231 participants in each arm. We estimate that 10% of participants will not complete the project, so a total of 508 participants will be needed.

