### Outcomes

#### Primary outcome

Duration of illness and symptoms from an ARTI. The participant-reported primary outcome will be assessed as the number of days until a patient’s daily activities (e.g. work and recreation) are no longer restricted by symptoms from an ARTI. The non-inferiority margin between the intervention group and the control group is set at a one-day difference. The recovery measure will be the specific day indicated by the participants using the validated ARTIQ.

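### The stated sample-size inputs require 288 per arm, not 231; at one-sided alpha 0.025 the planned trial has about 76% power, not 85%

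*Protocol article*

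**What the plan says.** The Sample size section of the protocol article gives every input and the result.

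- **Variability:** from a comparable earlier trial, "the number of days when patients experienced restrictions from an ARTI had a standard deviation of 4 days".
- **Margin:** the design "allows for a clinical non-important difference in sickness of max. 1 day in the PCT group compared to the standard care group". The Primary outcome section agrees: "The non-inferiority margin between the intervention group and the control group is set at a one-day difference".
- **Expected duration:** "We expect an ARTI to last on average 9 days". This is one figure for the condition; no difference between the arms is assumed anywhere.
- **Error rates:** "The power (1-β) is set at 85% and α at 0.025 (non-inferiority study design".
- **Result:** "The two arms of the study will be randomized 1:1 with 231 participants in each arm".
- **Allowance for loss:** "We estimate that 10% of participants will not complete the project, so a total of 508 participants will be needed".

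The Abstract repeats the total of 508, and the design section repeats the one-day limit.

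**The concern.** The inputs and the result stand in the same paragraph and should agree by the usual formula for non-inferiority of two means. They do not: the stated number per arm is about 20% below what the inputs require (231/288 = 0.80).

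The primary outcome is the number of days until daily activities are no longer restricted, and showing that this is not prolonged by a day or more is the trial's main argument that withholding antibiotics is acceptable. If the decision is made at the stated alpha, the trial is more likely than advertised to end without a conclusion even when the PCT strategy is truly no worse. The paragraph also leaves unclear which alpha governs the decision, and this should be settled before the data are analysed.

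**Working it through.** **Inputs (Sample size section):** SD 4 days, margin 1 day, power 85%, alpha 0.025, 1:1 allocation, 10% loss.

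**Assumptions:** true difference 0, because no other is stated; alpha 0.025 read as one-sided, because the article ties it to the non-inferiority design.

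**Formula:** n per arm = 2 × SD² × (z for 1 − alpha + z for power)² / margin² = 32 × (z for 1 − alpha + 1.036)².

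**1. Trying to reproduce 231**

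| Setting (SD 4, margin 1) | Calculation | n per arm |
|---|---|---|
| One-sided 0.025, 85% power (as stated) | 32 × (1.960 + 1.036)² = 287.3 | 288 |
| One-sided 0.05, 85% power | 32 × (1.645 + 1.036)² = 230.06 | 231 |
| Two-sided 0.025, 85% power | 32 × (2.241 + 1.036)² = 343.8 | 344 |
| One-sided 0.025, 80% power | same formula | 252 |
| One-sided 0.025, 90% power | same formula | 337 |

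The stated figure is not reproduced at the stated alpha. It is reproduced exactly at one-sided 0.05. The noncentral t distribution gives 289 and 231 for the first two rows, so the choice of normal or t calculation does not explain the gap.

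**2. Power at the stated alpha (one-sided 0.025)**

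Power = Φ(margin / SE − 1.960), with SE = 4 × √(2/n).

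- 231 per arm: SE = 0.3722, 1/0.3722 = 2.687, and Φ(0.727) = 76.6% (76.5% by noncentral t).
- 508 enrolled less 10%: 508 × 0.9 = 457.2, or 228.6 per arm. SE = 0.3741, and Φ(2.673 − 1.960) = 76.2%.
- 508 enrolled with no loss, 254 per arm: SE = 0.3549, and Φ(2.817 − 1.960) = 80.4%.

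Even complete follow-up of all 508 does not reach 85%. At one-sided 0.05, 231 per arm would give Φ(2.687 − 1.645) = 85.1%.

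**3. Allowance for loss**

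- 2 × 231 = 462, and 462 × 1.10 = 508.2, which is the stated 508.
- To keep 462 after a 10% loss: 462 / 0.90 = 513.3, so 514.
- 508 leaves about 457, five short of 462. The effect on power is 76.6 − 76.2 = 0.4 percentage points.

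**4. What the stated parameters would need in full**

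2 × 288 = 576 evaluable, and 576 / 0.90 = 640 enrolled.

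**The case against.** The strongest reply is that 231 can be reached at one-sided 0.025 with 85% power if another input differs: an SD of about 3.59, or a true advantage of about 0.12 day for the PCT arm. The SD is printed as a whole number and might be rounded; an SD of 3.5 would need only 220 per arm. This stands as a caution about the cause. It does not rescue the paragraph, which says SD 4 and gives no assumed difference, so the figures as printed still disagree.

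A second reply is that alpha is not called one-sided in words. A two-sided reading raises the requirement to 344 and widens the gap. Nor does the condensed form of an article help, since nothing is missing here: inputs and result are both printed.

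Four stronger readings are tempting and are not supported.

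- **That the calculation was certainly run at 0.05.** The exact match makes this likely, but the article does not say so.
- **That alpha was halved once too often.** One-sided 0.0125 gives 344 per arm, so this error would make the trial larger, not smaller.
- **That the false non-inferiority rate is double the stated one.** This would follow only if the decision were taken at one-sided 0.05, and nothing in the article says it will be. At 0.025 the type I error is as stated and the harm is lost power.
- **That covariate adjustment restores 85%.** This needs covariates explaining about 20% of the variance (1 − 228.6/287.3 = 0.20). That figure is solved backwards from the shortfall, and the article gives no value for site, age, sex or any other covariate.

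**Conclusion.** The error stands as a contradiction within one paragraph. On the stated inputs the requirement is 288 per arm against 231 planned, and power at one-sided 0.025 is about 76%, roughly 9 percentage points below the stated 85%. This rests on a true difference of zero, an SD of exactly 4 days, a comparison of means and a one-sided reading of alpha.

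A mislabelled alpha is the probable but unconfirmed explanation. The allowance for loss is a separate, minor slip. The consequence is a higher chance of an inconclusive trial; the mismatch does not by itself bias the comparison or inflate the false-positive rate.

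**What to change.** Keep one-sided alpha 0.025, with non-inferiority concluded when the upper limit of the two-sided 95% confidence interval for the difference (PCT minus control) lies below 1 day. Restate the paragraph to say that, with SD 4 days, a margin of 1 day and no true difference, 508 enrolled and about 457 evaluable give about 76% power. State the assumed true difference and the sidedness of alpha in words, and either report the 457 or correct the inflation to 514.

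If one-sided 0.05 was in fact intended, declare it as the alpha and align the interval with it (two-sided 90%). The change should not be made silently.

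If the sponsor prefers to keep both 0.025 and 85%, the target is 288 per arm, or 640 enrolled, which is 132 more than 508. The Time plan reports recruitment as paused, so this was still open when the article was written.

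Any gain from covariate adjustment should appear only as an assumption with a range. Dividing 228.6 by (1 − R²) gives these powers at one-sided 0.025:

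- R² = 0: 76.2%
- R² = 0.05 (effective n 240.6): Φ(2.742 − 1.960) = 78.3%
- R² = 0.10 (effective n 254): 80.4%
- R² = 0.20 (effective n 285.75): Φ(2.988 − 1.960) = 84.8%

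The restatement costs one paragraph and a less favourable power figure, with no extra participants.

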#### Statistical analysis

An intention-to-treat (ITT) and a per-protocol (PP) analysis are planned. Chi-square tests for binary effects and t-test or Mann-Whitney U-test for interval scale effects will be used (depending on distribution).

We will also present descriptive statistics in the different subgroups such as sex, age, and demographic variables.

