## Methods/Design

### Design, setting and randomization

This study is a randomized, single-blinded, non-inferiority, multi-practice intervention study comparing a PCT group to a control group. We expect the mean duration of ARTI symptoms to be approximately 9 days [21, 22] and we want to detect if this increases to > 10 days in the PCT group i.e. a non-inferiority limit of one day.

The PARI project is a single-blinded study as participants will not be informed of their allocation group: standard care or PCT group. GPs will have access to the PCT results for the intervention group. GPs can tell patients if the biomarker suggests whether antibiotics are needed or not. This is based on the CRP results for both groups and, in the intervention group only, also the PCT levels. Patients will be informed only that “the biomarker” suggests relevant treatment, and other similar generic statements; they will not be informed as to which biomarker the physician refers.

In case of accidental demasking, the investigator will report this as a protocol deviation.

If the PCT level is above 2 ng/L, demasking will deliberately take place because the GP will have to consider referring the patient to hospital on suspicion of serious infection.

At least five practices in two different regions of Denmark, The Capital Region and Region Zealand, will recruit participants, representing both urban and rural areas.

Randomization will be performed by a remote internet-based randomization tool (sealedenvelope.com). The allocation sequence will be stratified by site, age and sex.

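### The primary outcome's test is chosen by distribution from a t-test or a Mann-Whitney U-test, and neither is tied to the one-day margin, which is set in mean days

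*Protocol article*

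**What the plan says.** The Design section describes the trial this way: "This study is a randomized, single-blinded, non-inferiority, multi-practice intervention study comparing a PCT group to a control group". It expects a mean symptom duration of about 9 days and continues: "we want to detect if this increases to > 10 days in the PCT group i.e. a non-inferiority limit of one day".

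The Primary outcome section defines the endpoint as "the number of days until a patient’s daily activities (e.g. work and recreation) are no longer restricted by symptoms from an ARTI" and adds: "The non-inferiority margin between the intervention group and the control group is set at a one-day difference".

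The Sample size section stays on the scale of the mean. It takes from a comparable study that restricted days "had a standard deviation of 4 days", says "We expect an ARTI to last on average 9 days", and states: "The power (1-β) is set at 85% and α at 0.025 (non-inferiority study design"). It arrives at 231 per arm.

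The Statistical analysis section plans intention-to-treat and per-protocol analyses and then gives one sentence on method for all outcomes: "Chi-square tests for binary effects and t-test or Mann-Whitney U-test for interval scale effects will be used (depending on distribution"). It does not treat the primary outcome separately, and it links neither test to the margin.

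**The concern.** The margin, the expected duration and the SD are all in mean days. The named analysis can leave that scale.

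- **The rank branch.** A Mann-Whitney test compares rank distributions. It does not yield a difference in mean days to set against one day, and the sample-size calculation does not describe it.
- **The switch.** If the distribution decides between a test on means and a test on ranks, the data decide which quantity the trial estimates. In a non-inferiority trial that quantity should be fixed in advance, because the margin has meaning only on its own scale.
- **No link to the margin.** Run in their default form, both tests address equality. Failing to reject equality does not show that a one-day excess has been excluded.

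At stake is whether the headline claim, that PCT guidance does not prolong illness by a day or more, rests on a test with the intended error rate.

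**Working it through.** **Inputs.** Margin 1 day (Primary outcome). Mean 9 days against a limit of 10 (Design). SD 4, power 85%, α 0.025 and 231 per arm (Sample size). The article does not say whether α is one-sided; I read it as one-sided because the design is non-inferiority.

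**1. The plan's own sample size.** For non-inferiority of means with a true difference of zero, n per arm = 2 × SD² × (z₁₋α + z₁₋β)² / margin².
- α 0.025: 2 × 16 × (1.960 + 1.036)² / 1² = 287.3, so 288 per arm.
- α 0.05: 2 × 16 × (1.645 + 1.036)² / 1² = 230.1, so 231 per arm.

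The stated 231 is reproduced at one-sided 0.05, not at 0.025. For the present point, what matters is that 231 comes out of a margin calculation on a difference in means.

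**2. A margin test on means at 231 per arm.**
- Standard error = 4 × √(2/231) = 0.372 day.
- Half-width of the 95% interval = 1.96 × 0.372 = 0.73 day.
- The upper limit is below 1 day when the observed difference is below 1 − 0.73 = 0.27 day.
- Power at no true difference = Φ(1/0.372 − 1.96) = Φ(0.727) = 76.6%. At one-sided 0.05 it is 85.1%.

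**3. Margin-shifted tests when the true mean excess is exactly 1 day.** The target rate for declaring non-inferiority is 2.5%. Simulation used 4,000 trials per setting, 231 per arm and control mean 9 with SD 4. The shapes are assumptions; the mean, SD and margin are the document's.

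| Shape | t-test shifted by 1 day | Mann-Whitney shifted by 1 day |
|---|---|---|
| Normal, location shift | 2.6% | 2.7% |
| Gamma, location shift | 2.7% | 2.7% |
| Gamma, all durations lengthened by 10/9 | 2.6% | 4.9% |
| Gamma, 10% of PCT patients delayed by 10 days | 2.4% | 13.5% |

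A repeat of the last two settings gave 4.5% and 14% for the rank test, and 2.1% to 2.5% for the shifted t-test. The t-test holds its level throughout. The rank test loses it when the effect is not a pure shift.

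**4. Conditional case: an equality test with non-significance taken as non-inferiority.** With a true excess of 1 day, SD 4 in both arms and 231 per arm, the two-sided 5% t-test is non-significant with probability Φ(1.96 − 1/0.372) = Φ(−0.727) = 23.4%. The lower-tail rejection is negligible. Simulation under normality gave 23% for the t-test and 25% for Mann-Whitney.

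**The case against.** The strongest reply is that the sentence names families of tests and does not state a null hypothesis. A two-sample t-test can be run against a one-day null or reported as an interval, and the margin, the non-inferiority α and the two planned analysis sets all suggest that this is intended. A condensed article may leave the decision rule to a full protocol or SAP that is not shown. This stands. The absent rule is therefore not the finding in itself, and the t-test branch can be made to serve.

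A reader might go further and infer that the trial plans an equality test and will take a non-significant result as showing no prolongation. The documents do not support that. No section says it. The Design wording about detecting an increase is loose, but the same sentence ends by stating the one-day limit. The 23% figure is therefore conditional.

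It can also be said that Mann-Whitney has an associated shift estimate in days (Hodges-Lehmann). That is true, but it equals the mean difference only under a pure location shift, which the article does not assume. Nor does the article show that the rank test is the likely choice: a mean of 9 and an SD of 4 do not prove skewness. It does keep that choice open.

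What the reply does not remove is the switch. The article fixes it explicitly, and a SAP that added a margin rule but kept the switch would still have the problem.

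**Conclusion.** The point holds in a limited form. The article lets the distribution move the primary analysis from means to ranks, while its margin and sample size are in mean days, and it ties neither test to the margin. It would be too strong to say that the stated analysis cannot answer the primary question, because a t-test against a one-day null, or its interval, would answer it.

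The firm part is the Mann-Whitney branch and the switch. Even in its most favourable, margin-shifted form, the rank test's false non-inferiority rate is about 4.5% to 14% instead of 2.5% under two assumed shapes: proportional lengthening, and late recovery in a minority. The size depends on those shapes. Under a pure location shift there is no inflation.

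The conditional error of about 23% applies only if a plain equality test were used and its non-significance misread. It assumes SD 4 in both arms and 231 per arm.

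Severity: should be fixed. Little text needs to change, and the primary conclusion depends on it.

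**What to change.** Give the primary outcome its own analysis sentence, for example: the difference in mean days (PCT minus control) will be estimated with a two-sided 95% confidence interval, t-based with unequal variances or with robust standard errors; non-inferiority will be declared only if the upper limit is below 1.0 day in both the intention-to-treat and the per-protocol analysis. Drop the distribution-dependent switch for this outcome and keep Mann-Whitney as a supportive description. If a full protocol or SAP already contains such a rule, confirm that it does not also retain the switch.

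The cost is one or two sentences, settled before the data are unblinded, with no added burden on participants.

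One downside must be disclosed. At α 0.025 read as one-sided, with SD 4 and 231 per arm, this rule has about 77% power, not 85%. The stated power would need 288 per arm, or 2 × 288 / 0.9 = 640 in total with 10% dropout. The shortfall comes from the sample-size section, not from the rule, and the two should be reconciled together.

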#### Safety

If the participant’s condition gets worse they will contact their own doctor or the doctor on call as in every other incidence.

Serious unexpected events and unexpected events that that occur during the study, regardless of allocation group, will be reported orally and in writing to the project coordinator who is responsible for follow-up on unexpected events.

The safety issues will be discussed at all PARI study board meetings.

### Ethical issues

The study and all participant-related information have been approved by the regional ethics committee.

All of the interventions being performed in the PARI study are already known and tested in previous trials or approved treatments.

The measurement of PCT level is done by way of a finger prick test collecting a small blood sample of approximately 20 µl. This kind of blood sampling is a common procedure in general practice, and troublesome unexpected events as a direct result of this procedure are unlikely to happen.

Unexpected events as a result of potential overtreatment with antibiotics are also not considered likely to happen in the context of already published literature [18, 19, 27].

### Time plan

The PARI project recruited the first patient in February 2020. It was estimated that recruitment of all patients would take 18 months. However, the COVID-19 pandemic has paused the study. In Denmark, patients with symptoms of ARTI were triaged by phone or sent directly to COVID-19 clinics in hospitals. Therefore, it is still unclear when we will be able to continue recruiting participants to the PARI project, however, it is expected fall/winter 2021.

## Discussion

The PARI project is, to our knowledge, the first study to examine a PCT POC test in general practice. Previous studies have examined PCT levels either in a hospital setting or in general practice with a venous blood sample and a prolonged wait for the result. GPs are familiar with POC tests (such as CRP and strep A tests) and these are valuable tools for decision-making in many cases. However, application of PCT as an add-on when an ARTI is not trivial (e.g. CRP values are above 20 mg/L), may aid the GP in ruling out a serious bacterial infection. This could in theory limit GP uncertainties and assist in targeting antibiotics only to the relatively few patients with a high probability of having a bacterial infection and likely to benefit from antibiotic treatment. If this study shows that the PCT-guided antibiotic treatment for ARTI can reduce the use of antibiotics with no safety concerns for the patients (i.e. prove non-inferiority), it will contribute to reaching national goals for improving the rational use of antibiotics in general practice and thereby reduce the development of antibiotic resistance.

Strengths of the study include the randomized controlled trial design that will provide a clear answer regarding the study’s primary objectives. A non-inferiority design has been chosen to examine whether a PCT POC test is not worse than standard care regarding patient safety and duration of symptoms. In addition, we expect PCT testing to reduce the number of antibiotic prescriptions.

There are some limitations to the study. First, the study is single-blinded, i.e. patients are unaware of the treatment group to which they have been randomized. This is important to minimize reporting bias in the PARI trial as the primary outcome is a patient-reported outcome (recovery). It is impossible in this setup to blind GPs since they need to know which group the patient is randomized to as part of the clinical decision-making process. This information bias could lead to the GP learning from the results of the PCT test and thereby improving their clinical judgement. However, we do not believe such a bias will significantly change the results of the study and the direction of the bias would likely be conservative. Second, the GPs who opt to be included in this study may be more motivated and interested in research and they may be more reluctant to prescribe antibiotics in general, compared to other GPs. This kind of selection bias could affect the results. However, the direction of this bias is also likely to be conservative.

Another limitation to consider is that the analysis of a PCT POC test takes 20 min compared to the CRP measurement, which only takes a couple of minutes. In this study setting we do not consider this a problem, but in the longer term, it could affect the practical use and possible implementation of findings on a wider scale in general practice.

In conclusion, the PARI study is, to our knowledge, the first to examine a PCT POC test in general practice aimed at reducing the use of antibiotics in patients with symptoms of ARTI, without prolonging the symptoms and the duration of restrictions to patients’ daily lives. Since antibiotic resistance is a worldwide health problem, we believe that the results of this study could help to better target antibiotic treatment only to those patients with bacterial infections, which in turn will contribute to limiting antibiotic resistance.

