Procalcitonin (PCT) is a precursor protein that occurs at very low levels in the blood under physiological conditions [15]. It is, however, correlated with high levels in the blood in cases of serious bacterial infection. It also has a shorter time of release, a shorter half-life than CRP and it is less sensitive to surgery and non-bacterial infection [16, 17]. Studies from general practice have to date shown a reduction in the prescription of antibiotics by PCT-guided antibiotic treatment without significantly prolonging the duration of restrictions in patients’ daily lives due to infection [18, 19]. However, these studies were performed without a PCT point-of-care(POC) test and the test result was not available until hours after the initial patient assessment because it was sent for analysis in a hospital laboratory. Further, these studies were performed in an era when CRP-guided antibiotics were not systematically established.

To our knowledge, the Procalcitonin-guided Antibiotics in Respiratory Infections (PARI) trial is the first to examine a PCT POC test in general practice. The POC element of the intervention may be of crucial importance, since it makes a PCT-guided antibiotic intervention logistically realistic in a primary care setting for the first time.

The aim of this study is to determine whether it is possible to lower the use of antibiotics in patients presenting to their GP with symptoms of ARTI, without significantly prolonging the period of illness by using a PCT POC test.

The PARI study aim is in line with Danish national goals to improve the rational use of antibiotics in general practice [20].

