#### Secondary outcomes

These are the outcomes to be assessed regarding antibiotic treatment and clinical measures of treatment failure:

Number of participants in each trial arm exposed to antibiotic treatment at index consultation (day 1) and within 30 days.Number of participants in each trial arm with side effects from antibiotic treatment within 14 days.Number of participants in each trial arm with re-consultations within 30 days.Number of participants in each trial arm admitted to hospital (including diagnosis and mortality) within 30 days.Characterization of biomarker (CRP and PCT) level at index consultation..

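### The Discussion claims non-inferiority on patient safety, but the only margin, alpha and power are for days of restricted activity; the joint aim of fewer antibiotics also lacks a stated link to the conclusion

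*Protocol article*

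**What the plan says.** **Aim (Background).** The study sets out to "determine whether it is possible to lower the use of antibiotics in patients presenting to their GP with symptoms of ARTI", on condition that illness is not significantly prolonged. The conclusion at the end of the Discussion repeats this pairing.

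**Primary outcome.** This is the "number of days until a patient’s daily activities (e.g. work and recreation) are no longer restricted by symptoms from an ARTI", reported by the participant. "The non-inferiority margin between the intervention group and the control group is set at a one-day difference". The Sample size section bases 231 per arm on that margin and on a cited trial in which such days "had a standard deviation of 4 days". No other outcome has a margin or a power.

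**Secondary outcomes.** The first listed is "Number of participants in each trial arm exposed to antibiotic treatment at index consultation (day 1) and within 30 days". Side effects, re-consultations, and hospital admission (including mortality) follow. The Statistical analysis section names chi-square tests for binary outcomes.

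**Discussion.** The result sought is that PCT-guided treatment "can reduce the use of antibiotics with no safety concerns for the patients (i.e. prove non-inferiority"). The next paragraph says the design was chosen to examine "whether a PCT POC test is not worse than standard care regarding patient safety and duration of symptoms". A fall in prescribing is then added as something the authors expect.

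**The concern.** Two statements in the Discussion give the design a property it does not have. One says that non-inferiority covers patient safety. The other treats an absence of safety concerns as the same thing as proving non-inferiority. Days of restricted activity measure recovery, not admission or death. A trial can meet its one-day margin and still say very little about whether withholding antibiotics led to rare serious outcomes. If the wording reaches the final report, readers will take safety as formally demonstrated.

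A smaller matter is the joint aim. An add-on test that leaves illness duration unchanged is of interest only if it also lowers antibiotic use. The article has the right outcome and a test for it, but does not say which of the two exposure time points carries the claim, or that the conclusion depends on it.

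**Working it through.** **1. The plan's own sample size.** Inputs from Sample size: margin 1 day, SD 4, power 85%, alpha 0.025. The true difference is taken as 0.

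n per arm = 2 × SD² × (z_alpha + z_power)² / margin²

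- One-sided 0.025: 32 × (1.960 + 1.036)² = 287.3, so 288.
- One-sided 0.05: 32 × (1.645 + 1.036)² = 230.1, so 231.

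The stated 231 is reproduced at one-sided 0.05, not 0.025. That is a separate matter; both alphas are carried below. With 10% added, 462 × 1.10 = 508.2, which matches 508 (254 per arm).

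**2. Chance of meeting the margin if PCT changes no prescribing.** Assume PCT can affect duration only through prescribing, so the true difference is 0. With 231 per arm:

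- SE = 4 × √(2/231) = 0.372, and 1/0.372 = 2.687.
- One-sided 0.025: Φ(2.687 − 1.960) = 77%.
- One-sided 0.05: Φ(2.687 − 1.645) = 85%.

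**3. What 231 per arm can say about admission.** The article gives no rate, so 1%, 2% and 5% are assumed.

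- Half-width = 1.96 × √(2p(1 − p)/231).
- Power to detect p against 2p (two-sided 5%) = Φ[(d − 1.96 × SE0)/SE1], where SE0 uses the pooled proportion and SE1 the separate ones. At 1%: (0.01 − 1.96 × 0.01131)/0.01130 = −1.08, so 14%.
- For scale, n per arm for non-inferiority with a margin equal to p (excluding a doubling), one-sided 0.025, power 85% = 2p(1 − p)(1.960 + 1.036)²/p².

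| Assumed rate | Expected events per arm | 95% half-width | Power, doubling | n per arm, margin = p |
|---|---|---|---|---|
| 1% | 2.3 | 1.8 points | 14% | 1,778 |
| 2% | 4.6 | 2.6 points | 24% | 880 |
| 5% | 11.6 | 4.0 points | 53% | 342 |

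These are normal approximations and are rough in the 1% row. The margin in the last column is illustrative, not a proposal.

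**4. Power for antibiotic exposure.** The article gives no control prescribing rate, so 30-70% is assumed, with the same power formula at two-sided 5%. Example at 231 per arm:

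- 0.50 against 0.35: (0.15 − 1.96 × 0.0460)/0.0455 = 1.32, so 91%.
- 0.50 against 0.40: (0.10 − 1.96 × 0.0463)/0.0461 = 0.20, so 58%.

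| Reduction | 231 per arm | 254 per arm |
|---|---|---|
| 15 points | 90-97% | 92-98% |
| 10 points | 58-70% | 62-74% |

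**5. Joint power at 231 per arm**, treating the two tests as independent (an assumption):

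- 15 points: 0.766 × 0.90 to 0.97 = 69-75% at one-sided 0.025; 0.851 × 0.90 to 0.97 = 77-83% at one-sided 0.05.
- 10 points: 0.766 × 0.58 to 0.70 = 44-54%; 0.851 × 0.58 to 0.70 = 49-60%.

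**The case against.** The strongest reply concerns antibiotics. A reader might infer that the article calls non-inferiority on duration a success by itself, or treats it as proof of fewer antibiotics. The text does not support this. The Discussion sentence is conditional on showing reduced antibiotic use, and the parenthesis most naturally explains the safety clause next to it. The aim and the conclusion both pair the two conditions. Antibiotic exposure is the first secondary outcome and has a named between-arm test. Making the outcome that could be harmed the powered primary is a defensible choice, and a testing order may sit in a full protocol or SAP not shown. All of that stands. What remains is that the article does not tie one named exposure endpoint to its joint aim, and step 2 shows why that link matters.

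On safety, it can fairly be said that admission, mortality, re-consultation and side effects are prespecified, that unexpected events are reported and discussed by the study board, and that the problem lies in two phrases of a Discussion. This limits the seriousness but does not remove the point: those phrases state what the design can prove, and no unseen analysis plan makes a one-day margin on restricted activity a margin on safety.

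**Conclusion.** The point holds for safety. Non-inferiority is defined for days of restricted activity only. With no safety margin there is no criterion by which PCT guidance could be declared not worse on safety. At assumed admission rates of 1-5% the trial is also too small to do so reliably: half-widths are 1.8 to 4.0 points and power to detect a doubling is 14-53%. These figures rest on assumed rates; the absence of a margin does not.

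This should not be stretched to say that even an event-free arm would be uninformative. With no admissions among 231, the one-sided 97.5% upper limit is 1 − 0.025^(1/231) = 1.6%, below a doubled rate of 2%.

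For antibiotics only a modest point survives: the joint aim should be written as a joint condition on a named endpoint. A reader might also infer that this addition is nearly free in power. It is not if the true reduction is nearer 10 points. Power of 58-74% then makes antibiotic exposure the limiting test, and the joint claim has materially less power than duration alone.

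**What to change.** 1. In the Discussion and any later report, limit the non-inferiority conclusion to duration of restricted activity. Remove the statements that non-inferiority shows PCT guidance to be not worse on safety or free of safety concerns.
2. Report hospital admission and death as risk differences with score-based 95% confidence intervals, without a non-inferiority claim.
3. State that support for PCT guidance requires both non-inferiority on duration and lower antibiotic exposure within 30 days. Test exposure at two-sided 5% as a gated key secondary, only after non-inferiority is shown. Exposure at day 1 is supportive. Since both must succeed in a fixed order, alpha is not split.
4. State the reduction in exposure that the trial is expected to detect, the assumed control rate, and the resulting power.

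Items 1 and 2 cost only wording; the data are already collected. Items 3 and 4 need no new data or participants, but lower the chance of the full claim. That cost is small to moderate for a 15-point reduction and substantial for 10 points, and should be stated openly.
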